## Abstract

This paper describes a protocol for a controlled laboratory study designed to evaluate how immersive real-time electromyographic (EMG) biofeedback affects standardized shoulder exercise performance and user experience in healthy adults. Participants aged 20–30 years will be randomly allocated to virtual reality (VR), mixed reality (MR), or a non-immersive control condition. Within the immersive arms, each participant will experience three EMG visualization modes (an anatomically mapped avatar, a dynamic bar display, and a live waveform graph) in randomized order. During five standardized shoulder exercises, bilateral deltoid activity will be recorded using six wireless EMG sensors, while three-dimensional kinematics will be captured with an optical motion-capture system. Outcomes will include joint-angle accuracy, normalized muscle activation, compensatory motion, range of motion, movement speed, task completion time, together with perceived exertion, simulator sickness, and system usability. By integrating synchronized EMG and motion-capture data with immersive feedback delivery, this protocol provides a reproducible framework for comparing VR and MR biofeedback environments and evaluating how visualization mode may influence exercise execution and user experience.•Compares VR, MR, and non-immersive shoulder exercise conditions.•Evaluates avatar, bar, and waveform EMG visualization modes.•Combines EMG, motion capture, and subjective assessments.

Compares VR, MR, and non-immersive shoulder exercise conditions.

Evaluates avatar, bar, and waveform EMG visualization modes.

Combines EMG, motion capture, and subjective assessments.

Specifications table

**Table utbl0001:** 

**Subject area**	Engineering
**More specific subject area**	Rehabilitation engineering; immersive biofeedback; electromyography-based exercise assessment
**Name of your protocol**	A Protocol for Assessing Virtual and Mixed Reality Environments with Real-Time Electromyographic (EMG) Biofeedback During Upper Limb Physical Exercises
**Reagents/tools**	Meta Quest 3 HMD (Meta Platforms, Inc.); Delsys Trigno Avanti wireless EMG sensors (SP-W06) with Trigno Research+ Base Station (SP-W02); Qualisys motion capture system (12 Arqus A5 + 2 Miqus video cameras); Adjustable dumbbells (2–5 kg); Resistance bands; Workstation (Intel i9–11900K, NVIDIA RTX 3060 Ti 8 GB GPU, 32 GB DDR4 RAM, Windows 11); Unity Engine 2022.3.18f1 LTS; Qualisys Track Manager 2024.3; Qualisys Unity SDK Package 12; Python 3.11
**Experimental design**	Randomized controlled mixed laboratory protocol. Participants will be allocated to one of three between-subjects groups: virtual reality, mixed reality, or non-immersive control. Participants in the virtual and mixed reality groups will complete the exercise protocol using all three EMG visualization modes (avatar, bar, and graph) in randomized order. Control participants will complete the same exercises without augmented feedback. Each participant will complete a single ∼120 min session involving five standardized shoulder exercises. The target population is healthy adults aged 20–30 years.
**Trial registration**	None
**Ethics**	This protocol involves human participants; informed consent will be obtained from all participants prior to data collection. Ethical approval was obtained from the Institutional Review Board (IRB) of the Faculty of Engineering, Ain Shams University, Egypt (IRB code: IRB-ASU-25-017). The study protocol, informed consent documents, and all participant-facing materials were reviewed and approved by the IRB.
**Value of the Protocol**	• Provides a reproducible framework for integrating real-time EMG biofeedback with immersive virtual and mixed reality environments during shoulder exercise assessment. • Enables systematic comparison of three visualization strategies (avatar, bar, graph) for presenting physiological biofeedback in immersive settings. • Combines synchronized multimodal data (EMG + motion capture) with standardized subjective assessments in a single controlled protocol.

## Background

Shoulder rehabilitation and exercise-based shoulder assessment depend on accurate exercise performance to restore strength, range of motion, and function, yet correct technique is often difficult to maintain outside supervised settings. This challenge is especially relevant for shoulder disorders because reduced shoulder motion and strength can limit daily activities, while home-based rehabilitation technologies still require reliable ways to guide exercise quality and progression [[1], [2], [3]]. Conventional rehabilitation commonly relies on verbal instruction, intermittent observation, or motion-based feedback, which may provide limited real-time information about underlying muscle activation. As a result, individuals may complete the visible movement while using compensatory strategies, recruiting non-target muscles, or repeating suboptimal mechanics.

EMG biofeedback offers a way to make muscle activity visible during movement. In shoulder rehabilitation, systematic review evidence suggests that EMG biofeedback has been investigated for pain and function, but findings remain limited by small numbers of studies, heterogeneous protocols, and variable outcome measures [4]. Broader reviews of EMG combined with virtual or augmented reality also indicate that surface EMG can support rehabilitation applications as control or biofeedback, although standardized protocols remain limited [5]. Early systems combining EMG biofeedback with VR have focused mainly on upper-limb rehabilitation, usability, and task engagement rather than direct comparison of immersive delivery modes [6].

VR and MR offer more integrated ways to deliver feedback within the exercise experience. VR provides a fully computer-generated environment, whereas MR overlays digital content onto the physical environment, preserving visual access to the user’s body, equipment, and surroundings [7]. Both approaches are relevant to upper-limb rehabilitation because immersive environments can provide repetitive practice, salient feedback, task-oriented interaction, and motor-learning support [8]. Physiological measurements in VR may also support more objective and adaptive user-state assessment during immersive interaction [9].

A related unresolved issue is how EMG feedback should be visualized. Feedback design can influence attention, cognitive load, motor learning, and dependence on guidance [[10], [11], [12]]. Recent work on muscle-engagement visualization [13] and EMG-based interaction in VR further suggests that the body location, visual representation, and feedback modality can affect performance and workload [14]. However, the comparative effects of anatomically mapped avatar displays, abstract bar indicators, and live waveform graphs during shoulder exercises remain insufficiently understood.

Two methodological gaps, therefore, remain. First, direct comparisons between VR and MR for delivering real-time EMG biofeedback during shoulder exercises are limited. Second, few controlled protocols compare how different EMG visualization modes affect exercise execution and user experience. This protocol addresses these gaps by evaluating real-time EMG biofeedback during standardized shoulder exercises across VR, MR, and non-immersive conditions, while also comparing avatar-, bar-, and graph-based visualization modes. By combining objective kinematic and EMG outcomes with usability, exertion, and simulator-sickness measures, the study provides a structured workflow for quantifying exercise performance and user experience under controlled immersive biofeedback conditions.

## Description of protocol

### Study design

This study will use a controlled mixed experimental design. Participants will first be allocated to one of three between-subjects groups: (1) VR with real-time EMG biofeedback, (2) MR with real-time EMG biofeedback, or (3) a non-immersive control group that performs the same exercises without augmented feedback. This three-arm structure enables comparison between the two immersive delivery modes (VR vs. MR) and comparison between immersive biofeedback and conventional non-immersive exercise (VR and MR vs. control).

Within the VR and MR groups, each participant will experience all three EMG visualization modes: (1) an animated avatar with muscle-region highlighting, (2) a dynamic bar indicator, and (3) a live EMG waveform graph. The order of these visualization modes will be randomized for each participant to reduce order, learning, and fatigue effects. This within-participant visualization structure allows comparison of the three feedback formats while keeping the immersive delivery mode fixed for each participant. Participants in the control group will not receive visualization-format exposure because they perform the exercises without augmented feedback.

Randomization will be performed using a pre-prepared randomized allocation schedule designed to maintain balanced group distribution during recruitment. Participants will be assigned to the VR, MR, or non-immersive control group after eligibility confirmation and informed consent using a restricted randomization schedule with equal numbers of assignments arranged in randomized order. This ensures that participants are distributed evenly across the three study groups as recruitment progresses. For participants allocated to the VR and MR groups, the order of the EMG visualization modes will be randomized using a rotating visualization-order schedule. The avatar, bar, and graph modes will be assigned in different orders across participants so that the presentation sequence is balanced and order effects are reduced. Control participants will complete matched exercise blocks without EMG visualization. Group allocation and visualization-order records will be documented in the session log and stored separately from participant outcome files to maintain traceability.

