**Fig. 7 fig0007:**
[figure not shown]
Experimental protocol and procedures.•**Bar Mode:** Dynamic bar indicators show EMG amplitude for each monitored muscle.•**Graph Mode:** Scrolling waveform graphs display filtered EMG signals in real time.

In the VR condition, feedback will be displayed in a fully immersive virtual environment. In the MR condition, feedback will be overlaid onto the participant’s view of the physical laboratory using the headset’s passthrough cameras.

**Control Group:** Participants will perform the same exercises without augmented feedback and as 3 blocks matching the VR and MR group number of repetitions and rest periods, while wearing the same EMG sensors and motion-capture markers to maintain equivalent instrumentation burden.

During rest intervals, participants will complete brief in-session questionnaires, including the Borg Rating of Perceived Exertion (RPE) scale [18] to assess perceived effort for each exercise.

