#### Planned statistical analysis

Descriptive statistics will be used to summarize all objective and subjective outcomes. Continuous variables will be reported as mean ± standard deviation or median and interquartile range, depending on data distribution. For outcomes measured repeatedly across exercises and visualization modes, linear mixed-effects models will be used where appropriate, with participant included as a random effect and group, exercise, and visualization mode included as fixed effects. Model assumptions will be checked before analysis, and non-parametric alternatives will be used when required. Statistical significance will be set at (p < 0.05), with effect sizes and 95% confidence intervals reported where appropriate.

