## Limitations

•The single-session design precludes assessment of motor learning effects, skill retention, and long-term adherence outcomes that are critical for evaluating the clinical utility of immersive rehabilitation systems.•The exclusive focus on healthy young adults may limit the generalizability of findings to clinical populations with shoulder pathology, older adults, or individuals with physical or cognitive impairments relevant to rehabilitation.•Because participants in the VR and MR groups experience all three visualization modes in a single session, learning, fatigue, or carryover effects between visualization blocks may influence performance. Randomized visualization order and rest intervals are used to reduce these effects, but they cannot be fully eliminated.

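### The mode order is described both as randomized and as rotating, which may fix each mode's predecessor, and the stated model has no block term

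*Protocol article*

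**What the plan says.** Under Study design, the protocol article states the order scheme in three ways:

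- One sentence randomizes individually: "The order of these visualization modes will be randomized for each participant to reduce order, learning, and fatigue effects".
- A later one, on the two immersive arms, brings in rotation: "the order of the EMG visualization modes will be randomized using a rotating visualization-order schedule".
- The aim given for this schedule is balance: "The avatar, bar, and graph modes will be assigned in different orders across participants so that the presentation sequence is balanced".

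The number of distinct orders is not given. In the immersive arms "each participant will experience all three EMG visualization modes", so each of these participants has three blocks in one session. The description of Phase 4 has the control group exercise "as 3 blocks matching the VR and MR group number of repetitions and rest periods".

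Planned statistical analysis specifies linear mixed-effects models "with participant included as a random effect and group, exercise, and visualization mode included as fixed effects". Block, sequence and carryover are not among the named terms.

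Limitations accepts that "learning, fatigue, or carryover effects between visualization blocks may influence performance" and relies on randomized order and rest intervals to reduce these effects.

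**The concern.** Comparing avatar, bar and graph is one of the two gaps that the study sets out to address (Background). Two features put that comparison at avoidable risk.

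**Order list.** A rotation is systematic, whereas randomization for each participant is not, so a reader cannot tell which will be done. The most direct way to rotate three items gives avatar–bar–graph, bar–graph–avatar and graph–avatar–bar. Each mode then takes each position equally often, which meets the stated aim of a balanced sequence. But bar only ever follows avatar, graph only ever follows bar, and avatar only ever follows graph. What one mode leaves behind is charged to one particular other mode.

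**Model.** The article names learning and fatigue across blocks as threats, and it gives controls three matched blocks that carry drift information free of any mode effect. The listed fixed effects use none of this. Drift goes into the residual, and it can leak into the mode contrasts if the data become unbalanced.

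**Working it through.** **Inputs.** From the article: three modes, three blocks, and fixed effects for group, exercise and mode with a random participant effect. It gives no figure on this point to reproduce, and no sample size, SD or dropout rate. I therefore assume n = 30 immersive participants where a number is needed, and express results per unit of carryover L, drift d and residual variance σ². The check is least squares on one value per block with participant and mode terms, with and without block and first-order carryover.

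**1. Carryover bias.** Suppose only avatar carries over, by L, and this is not modelled. The bias in a mode's mean is L times the share of orders in which that mode directly follows avatar.

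| | Three cyclic orders | All six orders |
|---|---|---|
| Bar follows avatar | 2 of 3 | 2 of 6 |
| Graph follows avatar | 0 of 3 | 2 of 6 |
| Bias, bar − graph | 0.67 L | 0 |
| Bias, bar − avatar | 0.67 L | 0.33 L |
| Bias, graph − avatar | 0 | 0.33 L |
| Worst contrast | 0.67 L | 0.33 L |

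Adding a block term leaves these biases unchanged.

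**2. Cost of adjusting for carryover.** Variance of a pairwise mode contrast:

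- Unadjusted, either scheme: 2σ²/n = 0.067σ² at n = 30.
- Adjusted, three cyclic orders: 10σ²/n = 0.333σ², ratio 10/2 = 5.
- Adjusted, six orders: 2.5σ²/n = 0.083σ², ratio 2.5/2 = 1.25.

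The ratios do not depend on n. The design matrix has full rank in every case, so carryover is estimable under rotation, but poorly.

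**3. Block drift with complete, balanced data.** Every mode is in every position equally often, so linear or non-linear drift gives zero bias in the mode contrasts even without a block term. Adding block leaves the contrast variance at 2σ²/n. What is lost without it is precision. With drift d (in residual SD) per block:

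- Drift sum of squares per participant: d²[(−1)² + 0² + 1²] = 2d².
- Residual degrees of freedom: 3n − (n + 2) = 2n − 2.
- Extra residual variance: 2nd²/(2n − 2) = d²·n/(n − 1).
- At d = 0.5, n = 30: 0.25 × 30/29 = 0.259, about 26%.
- At d = 0.5, n = 12: 0.25 × 12/11 = 0.273, so the standard error rises by √1.273 = 1.13.

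If all five exercises are analysed jointly, the figure at n = 30 is 10nd²/(15n − n − 2 − 4) = 75/414 = 0.18.

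**4. Block drift when balance is lost** (no block term):

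- Incomplete rotation: bias of up to 0.2 of the per-block drift with 10 participants, 0.1 with 20.
- Orders drawn by simple randomization: chance bias with SD of about 0.41 of the per-block drift at n = 12 and 0.29 at n = 24.
- Late blocks lost, n = 30, linear drift: if 3 of the 10 participants who have graph last lose block 3, the graph contrasts are biased by 0.17 of the per-block drift; if 5 of 10, by 0.30. With a block term both biases are 0. If losses fall equally on the three modes, the bias is 0 without it too.

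**The case against.** **The three-order rotation is inferred.** A schedule that cycles through all six orders fits the text as well, and a rotating list can be entered at random. A condensed article may also leave the number of orders to a fuller document. This stands: the constant predecessor is conditional. What remains is that the section describes the order in two ways that need reconciling.

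**The tempting stronger claim is wrong.** A reader might infer that fatigue and carryover cannot be separated from mode. The design does not support that. A complete rotation balances position, so drift is orthogonal to mode and block is estimable. Carryover is estimable too, though imprecisely under three orders. Nor do six orders abolish carryover bias: they halve the worst case and spread it over two contrasts.

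**Block and carryover terms often belong in the statistical analysis plan, and orders are to be recorded.** This stands in part. A plan not shown may add them, and block could be added later without changing the design. But the article does list its fixed effects, and block is not among them despite the threats it names. The predecessor structure cannot be repaired after data collection.

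**The risk is disclosed, and rests are provided.** True. Disclosure does not improve an order list or model that can still be changed.

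**Loss of late blocks is conjecture.** No rate is given, so the sizes in step 4 are illustrations. The article does allow trials to be stopped for fatigue or simulator sickness symptoms and excluded for technical failure. It stops trials rather than whole blocks, so the bias may be smaller than shown.

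**Conclusion.** The concern holds as a cheap improvement. The two descriptions of the mode order must be reconciled. If three cyclic orders are meant, the worst carryover bias is 0.67 L instead of 0.33 L, and carryover adjustment costs a five-fold variance instead of 1.25-fold. If all six orders are already used equally, only the wording conflict and the block term remain.

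Leaving out block does not bias the mode contrasts with complete, balanced orders. It inflates the residual variance by about 26% at a drift of 0.5 residual SD per block in the three-period layout (about 18% with five exercises analysed jointly). It also leaves the contrasts open to bias when late-block trials are lost unevenly across modes.

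These sizes assume first-order carryover from a single mode, 30 immersive participants for the residual-variance percentages and the lost-block examples, and linear drift for the lost-block figures. The article gives neither L nor d, so the absolute size of any bias is unknown.

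**What to change.** - **Study design:** replace the two descriptions with one. Use all six orders equally, assigned in randomly permuted sets of six, separately within VR and within MR.
- **Planned statistical analysis:** add block (1 to 3) as a fixed effect, and include the three control blocks so that they contribute to the drift estimate.
- **Sensitivity analysis:** report mode contrasts adjusted for first-order carryover.

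The cost is a new order list and one model term. Immersive group sizes are best kept in multiples of six. With complete, balanced data the block term costs nothing in contrast variance.

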### Setting

The study will be conducted at the Human Centered Mechatronics (HCM) Lab, located within the Virtual Hospital at Ain Shams University, Cairo, Egypt.

### Participants

#### Inclusion criteria

Participants will be eligible for inclusion if they meet all of the following criteria:•Healthy adults aged 20 to 30 years•No known history of shoulder injuries, pain, or movement disorders•Normal or corrected-to-normal vision (to ensure adequate visibility of VR and MR displays)•Ability to perform shoulder exercises at or above shoulder height without pain or restriction•Not currently engaged in regular, intensive shoulder-specific training or rehabilitation programs

#### Exclusion criteria

Participants will be excluded if they meet any of the following criteria:•Any diagnosed upper limb musculoskeletal or neurological impairment, or any uncorrected visual impairment (i.e., not correctable by standard glasses or contact lenses)•History of motion sickness or significant discomfort when using VR or MR headsets•Inability or unwillingness to wear EMG sensors or motion-capture markers•Any other medical or physical condition that, in the judgment of the research team, could pose a risk or confound results

### Equipment and instruments

The experimental setup will include an immersive display, motion-capture, EMG sensing, exercise, and computing components, as shown in Fig. 1.•**Immersive display:** The Meta Quest 3 headset (Meta Platforms, Inc., Menlo Park, CA, USA) will be used for both VR and MR conditions. It provides standalone operation, inside-out tracking, high-resolution display, and full-color passthrough for MR feedback.•**Motion capture:** Kinematic data will be captured using a Qualisys motion-capture system with 12 Arqus A5 and 2 Miqus video cameras arranged around an approximately 10.0 × 6.0 × 2.5 m capture volume. Cameras will be positioned approximately 2.9 m above the floor and angled inward/downward to maintain shoulder-marker visibility. Calibration will use an L-frame and T-wand, with a target residual error below 0.5 mm. Cameras will be synchronized at 300 Hz. Reflective markers will follow the Qualisys Sports Marker Set to compute joint angles, range of motion, velocity, and smoothness metrics.•**EMG:** EMG data will be collected using six Delsys Trigno Avanti wireless sensors (Delsys Inc., Natick, MA, USA; Model SP-W06) connected to a Trigno Research+ Base Station (Model SP-W02). EMG will be sampled at 1926 Hz using the 20–450 Hz bandwidth setting. EMG and motion-capture recordings will be synchronized using a hardware TTL synchronization signal generated by the Qualisys Camera Sync Unit.•**Exercise equipment:** Adjustable dumbbells (2–5 kg) and resistance bands of varying resistance levels will be used for exercise tasks and maximum voluntary isometric contraction (MVIC) calibration.•**Computing infrastructure:** Data acquisition, VR and MR application development, and real-time signal processing will run on a workstation with an Intel i9–11900K processor, NVIDIA RTX 3060 Ti 8 GB GPU, 32 GB DDR4 RAM, and Windows 11. All data will be stored on secure, password-protected systems within the HCM Laboratory.

